#### Descriptive analysis

2.9.1

Demographic characteristics of neonates and patterns of antibiotic use are summarized across study phases using descriptive statistics.

#### Time series analysis

2.9.2

Monthly aggregated data are used as the analytical unit. Statistical process control P charts are applied to assess temporal changes in antibiotic use rates and to identify special-cause variation based on standard run chart rules.

#### Interrupted time series analysis

2.9.3

Segmented regression models are used to perform ITS analyses for primary outcome measures, estimating both immediate changes in level following intervention implementation (level change) and changes in trend over time before and after the intervention (slope change). Effect estimates are reported with 95% confidence intervals.

#### Adjustment for center-level variation

2.9.4

To account for potential center-level heterogeneity, center-specific baseline characteristics, including local antibiograms and baseline hospital-acquired infection rates, will be considered in stratified analyses. Intervention adherence rate will also be summarized at the center level and incorporated into the interpretation of between-center differences in observed intervention effects. Where appropriate, mixed-effects models or sensitivity analyses will be performed to evaluate the robustness of intervention effect estimates after accounting for participating centers and relevant center-level factors.

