#### Data elements and sources

2.8.1

All participating centers collect data across three domains:

Baseline data: Data will be extracted from hospital electronic medical record systems and discharge summaries. Demographic and baseline clinical characteristics of enrolled neonates from both the pre-intervention (historical control) period and the intervention period will be collected, including sex, gestational age, birth weight, admission diagnoses, and comorbidities. In addition to patient-level data, center-level baseline characteristics will be collected for each participating NICU. These characteristics will include local microbiological resistance patterns (antibiograms) and baseline rates of hospital-acquired infections. These data will be used to describe inter-center differences that may influence empirical antibiotic prescribing practices.Process data: collected to calculate process measures, primarily using a standardized Antibiotic Use Case Registry Form. Key variables include a unique study identifier, date and indication for antibiotic initiation, completion of initiation assessment, documentation of the 48–72-h reassessment, and dates and results of blood cultures and other microbiological tests.Outcome data: collected to derive primary and balancing outcomes and extracted from electronic medical records and discharge summaries. These include daily antibiotic administration records (used to calculate antibiotic days), total length of NICU stay, dates and diagnostic basis of LOS, dates and causes of death, and records of antibiotic re-initiation following discontinuation.

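### The stated adjustment covers centres and fixed centre features only; a change over time in the mix of infants, measured in both periods, is described but not adjusted for in the interrupted time series

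*Protocol article*

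**What the plan says.** All references are to the protocol article.

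- **Section 2.9.4** states its aim as "To account for potential center-level heterogeneity". Under it, "center-specific baseline characteristics, including local antibiograms and baseline hospital-acquired infection rates, will be considered in stratified analyses". Where appropriate, mixed-effects models or sensitivity analyses examine the robustness of the effect estimates "after accounting for participating centers and relevant center-level factors". No infant-level factor is named.
- **Section 2.8.1** collects infant-level data in both periods, "including sex, gestational age, birth weight, admission diagnoses, and comorbidities". Of the antibiograms and baseline infection rates it says: "These data will be used to describe inter-center differences that may influence empirical antibiotic prescribing practices".
- **Section 2.9.1** gives the only stated use of the infant-level data: "Demographic characteristics of neonates and patterns of antibiotic use are summarized across study phases using descriptive statistics".
- **Section 2.9.3** describes segmented regression with a level change and a slope change, and names no covariate. Section 2.9.2 says "Monthly aggregated data are used as the analytical unit" without saying whether the series is pooled or by centre.
- **Section 2.6.2** treats high-risk preterm status as an indication to start antibiotics. The Figure 2 legend defines that status by gestational age together with perinatal risk factors.
- **Section 2.2** has all five units start together in April 2026.

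**The concern.** An interrupted time series without a concurrent control attributes to the intervention whatever departs from the projected baseline trend at the start date. Here all centres start in the same month, so no centre is left to show what would have happened otherwise. A step in the mix of infants around April 2026 would change the monthly rates without any change in prescribing.

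Prematurity bears on antibiotic initiation in the study's own pathway, so such a step can reach both primary outcomes. Section 2.9 counts the programme as successful if a reduction in either primary outcome is observed, with better adherence and no rise in the balancing measures. It sets no minimum reduction, so a modest artefact could satisfy the effectiveness part, and a shift the other way could hide a true reduction.

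The Discussion credits the design with control of time-related confounding and concedes only unmeasured confounders. Changing case mix is time-related and it is measured, but the stated analysis does not use it.

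**Working it through.** The plan gives no figure for this point, so there is nothing to reproduce. The check sets the stated uses side by side and then illustrates size.

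**1. What each factor can address**

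| Factor | Varies by month? | Stated use | Addresses changing infant mix? |
|---|---|---|---|
| Antibiogram, baseline infection rate | No, a baseline feature of each centre | Stratified analyses | No |
| Centre | No | Mixed-effects or sensitivity models | No, but handles shifts in volume between centres |
| Gestational age, birth weight | Yes, in monthly aggregate | Descriptive summary by phase | Could, but not used |

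**2. Shift in volume between centres (handled if centre terms are fitted)**

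Change in pooled rate = gap between centres × share of patient-days moved. Gaps of 100 to 300 and shares of 5% to 10% are assumed.
- Low end: 100 × 0.05 = 5 per 1,000; 5/636 = 0.8%.
- High end: 300 × 0.10 = 30 per 1,000; 30/636 = 4.7%.

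Centre-specific series or centre terms remove this.

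**3. Shift in infant mix (not handled by the stated analysis)**

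Anchor: antibiotic utilization rate (AUR) of 636 per 1,000 patient-days in 2024 (Introduction). The stratum rates are assumed. With rate H in preterm or low-birth-weight infants, L in others, and share s of patient-days:

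AUR = L + (H − L) × s, so s = (636 − L)/(H − L), and a fall of d in s changes AUR by −(H − L) × d.

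For H = 800 and L = 500: s = 136/300 = 0.453, and d = 0.10 gives −300 × 0.10 = −30, or 4.7% of 636.

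| H / L (assumed) | s | fall of 5 points | 10 points | 15 points |
|---|---|---|---|---|
| 750 / 550 | 0.430 | −10 (1.6%) | −20 (3.1%) | −30 (4.7%) |
| 800 / 500 | 0.453 | −15 (2.4%) | −30 (4.7%) | −45 (7.1%) |
| 900 / 450 | 0.413 | −22.5 (3.5%) | −45 (7.1%) | −67.5 (10.6%) |

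A rise in the share gives the same figures with a plus sign.

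**4. Effect on inference**

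Simulation: 12 + 12 pooled months with the three-month preparation gap, no true effect, 800/500, residual monthly SD 25, SD of the monthly share 0.03, 4,000 runs per row, two-sided 5% test of the level change. The SDs are assumed.

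| Step fall in share | Level change, unadjusted | False positives, unadjusted | Level change, adjusted for monthly share | False positives, adjusted |
|---|---|---|---|---|
| 0 | −0.4 | 4.6% | −0.5 | 5.1% |
| 5 points | −14.7 | 8.8% | 0.3 | 5.1% |
| 10 points | −29.6 | 18.0% | 0.5 | 4.4% |
| 15 points | −44.8 | 36.5% | −0.5 | 5.0% |

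The adjusted columns are a best case: the model adjusts for exactly the share that generated the data, with independent errors.

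**5. How finely case mix can be handled (Table 1, 2024 admissions)**

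Total 862 + 524 + 395 + 872 + 484 = 3,137, or 261 per month. By centre: 395/12 = 33 in the smallest unit to 872/12 = 73 in the largest. If 5% to 10% were below 32 weeks (assumed), the smallest unit would have 1.6 to 3.3 such infants a month, against 13 to 26 in the pooled month. Standardising each centre-month would be unstable; the pooled month with broad strata is workable.

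**The case against.** The strongest reply is that section 2.9.4 does what it sets out to do. Its aim is heterogeneity, and stratifying on centre features is a legitimate, if weak, look at effect modification with five centres. The article is condensed and no analysis plan is shown; a descriptive use of gestational age does not rule out others. Segmented regression absorbs a steady drift in case mix in the baseline trend, so bias needs a step or a change of trend at the start date, and nothing in the documents predicts one. All of this stands, and it limits the point to an improvement of the stated method.

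It does not remove the point. The article gives adjustment its own section, names the covariates, and confines the robustness models to centres and centre-level factors. That allocation is stated, and it passes over the measured factor that can change over time.

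A reader might infer four stronger claims that the documents do not support:

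- *That the centre features cannot confound.* This holds within centre or with centre terms. In a single pooled series, centre volumes can shift (step 2), and the article does not say which series is used.
- *That the features are aliased with centre in the planned analysis.* Beside five fixed centre effects, time, level and slope (rank 8), adding two centre-constant covariates leaves the rank at 8. But the plan puts these features in stratified analyses and names mixed-effects models, where they are estimable from five values. A feature-by-period interaction is also estimable beside centre main effects (rank 9).
- *That the robustness analysis removes no bias.* Accounting for participating centres removes bias from shifts in volume between them.
- *That case mix is the main source of confounding.* Nothing in the documents ranks it. It is one measured potential source.

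**Conclusion.** The point holds in limited form and is worth a change. The stated adjustment deals with differences between centres; it does not deal with a change over time in the infants admitted, although the needed variables are collected in both periods and prematurity bears on antibiotic initiation in the study's own pathway.

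The size of any bias cannot be obtained from the documents. Under the assumed stratum rates, a 5- to 15-point fall in the preterm share would produce a false change of −10 to −67.5 per 1,000 patient-days (1.6% to 10.6% of 636), and a rise would mask a true reduction of the same size. This rests on a step in mix coinciding with April 2026, which is possible but not shown. A full analysis plan, not available here, might already include a case-mix term; if so, the article should say so.

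**What to change.** In sections 2.9.3 and 2.9.4:

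1. Fit the interrupted time series on centre-month data with centre terms, with admissions as the denominator for the antibiotic use rate and patient-days for the AUR.
2. Prespecify a case-mix-adjusted series, at least as a key sensitivity analysis. Either add one or two monthly terms (for example proportion preterm, mean gestational age or mean birth weight), or standardise to the 2025 gestational-age mix, using broad strata on the pooled month rather than on each centre-month.
3. Report adjusted and unadjusted estimates side by side, and interpret a material difference before claiming an effect.
4. Keep the stratification by antibiogram and baseline infection rate, labelled as exploratory heterogeneity.

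Cost: one or two degrees of freedom and a little more analysis work. The variables are already in the data collection. If case mix does step at the start date, the adjusted level change will be less precise because the two are correlated; that loss reflects real uncertainty.

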## Discussion

3

This protocol explores strategies for optimizing antibiotic prescribing in resource-limited regional medical centers. Although global evidence regarding ASPs in NICUs is expanding, existing success stories are predominantly concentrated in elite teaching hospitals in high-income countries, which often rely on sophisticated rapid pathogen diagnostics and dedicated multidisciplinary teams (25, 26). In contrast, within the extensive network of municipal-level hospitals in China, antibiotic utilization rates have remained persistently high due to relatively constrained diagnostic resources and the prevalence of defensive medical practices in clinical settings (14, 27). This study uses a multicenter ITS design to evaluate the potential of a structured ASP intervention to reduce NICU antibiotic use while maintaining safety. Validating this localized intervention strategy will not only address the antibiotic burden in the Suqian region but also provide critical empirical evidence for antimicrobial stewardship pathways in resource-limited environments.

The proposed intervention components are designed to systematically optimize stewardship workflows through multi-level synergy. At the structural level, we established a two-tier governance framework—comprising a regional steering committee and hospital-level core implementation teams—to ensure the unified dissemination and localized execution of standardized protocols and decision-support tools. This structure, supported by monthly collaborative meetings, facilitates continuous data feedback and peer review, thereby ensuring core implementation fidelity across multiple centers. At the procedural level, the intervention centers on the standardization of clinical decision-making. The EOS Risk Assessment and Antibiotic Management Clinical Pathway, developed based on national evidence-based consensus (23), utilizes risk stratification to clarify indications for antibiotic initiation, reducing overuse driven by ambiguous clinical interpretations. Furthermore, the mandatory 48–72-h reassessment mechanism establishes a critical “decision checkpoint,” requiring clinicians to actively re-evaluate treatment plans based on emerging evidence, providing institutional support for minimizing unnecessary treatment prolongation.

Regarding the decision-making environment, previous studies have highlighted the high prevalence of defensive medical behaviors in Chinese clinical practice, often linked to strained patient-physician relationships and concerns regarding medical litigation (27–29). In resource-limited contexts lacking rapid, high-precision diagnostics, clinicians may prefer empirical antibiotic therapy as a risk-aversion strategy rather than relying solely on evidence-based indications. By providing standardized clinical pathways and structured decision support, this study offers clinicians clear, procedural frameworks for judgment, which may help mitigate the tendency toward excessive empirical prescribing driven by diagnostic uncertainty or legal concerns at the institutional level.

Globally, the vast majority of neonates receive care in regional centers similar to those in Suqian rather than in top-tier academic institutions. In such settings, where laboratory diagnostic capacity is relatively limited, the assessment of infection is often accompanied by higher uncertainty, and clinical practice is more prone to rely on empirical antibiotics for risk control (30). Consequently, the simple introduction of complex diagnostic technologies or educational guidelines is often insufficient to achieve sustained impact in daily practice. In contrast, a QI strategy that is clearly structured, embeddable into existing workflows, and does not significantly increase workload may better meet the practical needs of such environments. By simultaneously implementing and evaluating this intervention across multiple regional NICUs, this study provides a practical framework for other regions with similar resource profiles to explore stewardship improvement pathways.

Methodologically, the multicenter ITS design evaluates trend changes while controlling for time-related confounding (31). Moreover, the concurrent focus on primary, balancing, and process measures ensures a comprehensive assessment of the intervention's potential effectiveness and safety. However, this study has limitations. As a real-world QI initiative, the influence of unmeasured confounders cannot be entirely excluded. Additionally, the study's impact depends partly on the consistency of protocol execution and data quality across centers. Although the 12-month intervention period is sufficient for evaluating early level and trend changes within an interrupted time series framework, it may still be insufficient to fully assess the long-term sustainability of the intervention effect or to determine whether observed improvements can be sustained over time under routine practice conditions. Longer follow-up will therefore be important in future work. In addition, although AUR and DOT are widely used and highly comparable outcome measures in neonatal antimicrobial stewardship research, they do not fully capture differences in antibiotic spectrum intensity. Spectrum-based metrics such as antibiotic spectrum index or days of antibiotic spectrum coverage were not included in the present study because currently available scoring systems have not been adequately adapted or validated for neonatal populations, particularly with respect to common neonatal pathogens such as group B streptococci and coagulase- negative staphylococci (32, 33). Finally, this protocol does not include a formal cost-effectiveness analysis, which may be an important consideration for future large-scale implementation.

## Conclusion

4

This study proposes and systematically evaluates a multicenter antimicrobial stewardship QI program tailored for regional NICUs, addressing the persistent challenge of high antibiotic utilization in relatively resource-limited settings. By establishing a multi-tier governance structure, standardizing key clinical decision-making processes, and implementing continuous monitoring and feedback mechanisms, this study provides a pragmatic and reproducible pathway for optimizing neonatal antibiotic use in real-world clinical environments. Our approach highlights that through workflow restructuring and organizational synergy, antimicrobial stewardship can be effectively standardized without the necessity of highly complex technologies or substantial additional resource investment. The implementation experience gained from this study will serve as a reference for NICU stewardship interventions in similar resource contexts and lay the foundation for future evaluations of long-term impact and generalizability.
